### Data assessment

2.5

Data will be collected using a secure electronic Case Report Form (eCRF) within the REDCap platform. REDCap’s user-friendly interface and robust security features (hosted at the Department of Psychiatry, University of Münster, ensuring compliance with the General Data Protection Regulation (GDPR).

### Standardisation and training of study team in study assessments

2.6

To ensure data quality, consistency, and adherence to standardized procedures, a comprehensive training program will be implemented prior to the commencement of any study activities. This training program will address all aspects of data collection, assessment, and treatment delivery. Training materials will include detailed manuals and practice sessions, with assessment of competency at the end of the training. To ensure accuracy in the diagnosis of Major Depressive Disorder (MDD), all diagnoses will be confirmed by experienced clinicians. A communication system will be implemented to facilitate seamless communication, data sharing, and decision making among the research teams at the three collaborating institutions.

The comprehensive training, diagnostic confirmation, and established teleconsultation procedures will enhance data quality, minimize bias, and maximize consistency in the conduct of this multi- centre study.

### Primary and secondary outcome measures

2.7

The primary endpoint will focus on changes in depressive symptom severity, measured using primary MADRS, and secondary HAM-D and PHQ-9 especially in week 8. The use of multiple scales enhances the reliability and validity of the assessment, providing a more comprehensive picture of symptom change. Several secondary outcome measures will exploratively elucidate the impact of treatments on various aspects of patient well-being and functioning. These include side effects (UKU, GASE, MARS), quality of life and daily functioning (WHOQoL-BREF, GAF, FAST) as well as general health measures (e.g. lab tests). This comprehensive approach ensures that the study captures a broad range of outcomes, providing a robust and nuanced evaluation of the treatment effect and side effects of allopathic and Ayurvedic treatments for MDD. The question is exploratory in nature due to the design and methodology.

### Ethical considerations and data protection

2.8

Ethical considerations will guide all aspects of the study, from design and implementation to data analysis and dissemination. The research protocol was approved by the relevant Institutional Ethics Review Boards (IERBs) at participating institutions (MAM University approval number: MAM UNI/IECHR/2025; Bhaikaka University approval number: IEC/BU/162/Faculty/25/135/2025). In addition, the study was pre-registered with the Indian authorities (CTRI/2025/07/090147).

All potential participants will receive comprehensive information about the study’s purpose, procedures, risks, and benefits ensuring that participants can make an informed decision about their participation. Written informed consent will be obtained from all participants prior to any study procedures being undertaken. Participants will be free to withdraw their consent and discontinue their participation at any time without penalty. Participants will be closely monitored for the occurrence of adverse events throughout the study period. Regular follow-up visits will allow for the detection and assessment of any adverse effects, whether related to the study interventions or other factors. If any adverse events occur medical attention, adjustments to the treatment regimen, counselling, or other supportive measures as needed appropriate interventions will be provided promptly. Serious adverse events will be reported immediately to the relevant IERBs and the study team. The study will have a clear protocol for managing adverse events. A data safety monitoring board will regularly review safety data to ensure participant safety. The study’s data management procedures will strictly adhere to relevant data protection regulations, which includes GDPR Compliance, Indian Data Protection Standards, Local Data Safety Standards and Data Anonymization.

### Sample size calculation and statistical analysis

2.9

We hypothesise that all treatment groups lead to a statistically significant reduction in symptoms of depression between baseline and week 8 (within group effect). We also hypothesize that the groups do not differ in terms of treatment success (between group effect). We performed a power analysis to calculate the sample size. With a sample size of N = 105 patients, an alpha error probability of 0.5 and a moderate effect size (0.5) (for change in symptoms of depression), we achieve a statistical power of >0.8. An effect size of 0.5 equates to a mean difference in the MADRS score between baseline and week 8 of 50%, which reflects a commonly accepted clinical response measure in depression studies. In practise , this would mean a reduction of 15 points on the MADRS scale from 30 points at baseline to 15 points at week 8. Such a kind of reduction has been seen in other interventional studies in depression.

Data analysis will be conducted by the team at the Department of Psychiatry, University of Münster. The primary and secondary outcome measures will be analysed using an intention-to-treat (ITT) and exploratory approach. We will focus on specialized analyzation for longitudinal data. In addition, we will correct for confounding variables in all analyses where significant differences arise between the groups.

The choice of statistical test will depend on the nature of the data and the specific research question. For continuous outcome variables (e.g., scores on depression rating scales, quality of life scores, continuous physiological measures), Analysis of Variance (ANOVA) or independent samples t-tests will be used to compare means between the three treatment groups (Ayurvedic-only, Allopathic-only, and Combination). *Post-hoc* tests (e.g., Tukey’s HSD, Bonferroni correction) will be employed if significant differences are found between groups to determine which specific groups differ significantly. For categorical outcome variables (e.g., presence or absence of adverse events, categorical measures of quality of life, treatment adherence categories), Chi-square tests or Fisher’s exact tests (for small sample sizes) will be used to compare proportions between treatment groups. Given the repeated measures design (baseline, 8 weeks, 3 months, 6 months), appropriate statistical models for longitudinal data (e.g., repeated measures ANOVA, mixed-effects models) will be used to analyse changes in outcome measures over time within each treatment group and to examine the interaction effects between treatment group and time. This will allow for a more powerful examination of treatment effects and the assessment of treatment response trajectories. Strategies to address missing data will be carefully considered and documented. In addition to p-values, effect sizes (e.g., Cohen’s d) and 95% confidence intervals will be reported for all significant findings. All statistical analyses will be performed using appropriate statistical software packages (e.g., SPSS, R).

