**Methods:**

This six-month, naturalistic observational study will involve 105 adult participants (18–65 years) diagnosed with MDD according to DSM-5 criteria. Participants will be categorized to one of three groups: allopathic-only treatment (n=35), ayurvedic-only treatment (n=35), or a combination of both (n=35). Depressive symptom severity will be assessed as primary endpoint using primarily the MDRS, and secondarily HAMD and PHQ-9 scales at baseline, every 2 weeks until week 8, followed by monthly assessments until months 6. Secondary outcomes will exploratively include side effects (UKU, GASE, MARS), quality of life and daily functioning (WHOQoL-BREF, GAF, FAST) as well as general health measures (e.g. lab tests).

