Ayurvedic medicine, an ancient holistic system originating from India, offers an alternative and complementary approach to MDD (10). This system emphasizes the interconnectedness of mind, body, and spirit, aiming to restore balance through various interventions. These include herbal remedies (e.g., Ashwagandha, Brahmi etc.), dietary modifications tailored to individual constitution (Prakriti), lifestyle adjustments promoting holistic well-being, and mind-body techniques such as yoga and meditation (11). Ayurvedic treatment is well established in India. It is a holistic whole system approach that traditionally consists of specific components (Panchakarma, manual therapies Dietary Modifications, Herbal Formulations, Lifestyle Modifications, Sattvavajaya and Daiva-vyapasraya-cikitsa) that are integrated into a common treatment approach. There are special hospitals that specialize in such holistic treatment concepts. Patients can choose whether they want to be treated in an allopathic or an Ayurvedic hospital. While level A (e.g. meta-analysis and RCTs) and level B (evidence from at least one high-quality study or multiple moderate-quality studies) evidence studies and some smaller studies suggest the potential efficacy of Ayurvedic treatments in alleviating depressive symptoms (12–14), robust, large-scale randomized controlled trials comparing Ayurvedic treatment to allopathic treatments are relatively scarce (15). Understanding the mechanisms through which Ayurvedic treatment exert their effects on mood and related symptoms remains an area of active research.

This necessitates a more comprehensive understanding of the relative treatment effects, side effects and potential synergistic effects of integrating allopathic and Ayurvedic treatments for MDD. A comparative evaluation of these approaches is crucial for informing evidence-based clinical practice and optimizing therapeutic strategies for individuals experiencing this pervasive and debilitating disorder. This study aims to address this critical gap in the literature through observation and analysis of real-world outcomes of allopathic and ayurvedic treatment modalities for MDD.

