### Hypothesis and objectives

1.2

Based on the published literature, we assume that allopathic and Ayurvedic treatments are equally effective in treating depression, both leading to improvements in symptom severity. Therefore, we do not expect any statistically significant difference in treatment effect between the treatment groups (between-group effect) in week 8. However, we hypothesize that both therapies will lead to an improvement in depression symptoms over a period of 8 weeks (within-group effect). The question is exploratory in nature due to the design and methodology.

This study will pursue the following scientific objectives:

Treatment Effect: To quantitatively compare the effect of allopathic and ayurvedic treatments (and their combination) in reducing the severity of depressive symptoms in MDD, as measured by validated rating scales (primary Montgomery-Åsberg Depression Rating Scale (MADRS), secondary Hamilton Depression Rating Scale (HAM-D) and Patient Health Questionnaire-9 (PHQ-9) at baseline, 8 weeks, 3 months and 6 months.Side Effects and Quality of Life: To compare the incidence, type, and severity of adverse events associated with allopathic and ayurvedic treatments using standardized adverse event reporting like Udvalg for Kliniske Undersøgelser Scale (UKU), General Assessment of Side (GASE) and Medication Adherence Report Scale (MARS). Furthermore, to assess differences in quality of life (QoL) and daily functioning between treatment groups using validated QoL instruments (e.g., WHOQOL-BREF) and functional assessment scales (e.g., Global Assessment of Functioning (e.g., Global Assessment of Functioning (GAF) and Functional Assessment Short Test (FAST).General Health Evaluation: To evaluate and compare changes in general health parameters (e.g., Body Mass Index (BMI), vital signs, relevant blood work indicators such as liver and kidney function tests, electrolytes, CRP, leukocytes, red blood cells, platelets, haemoglobin , haematocrit , red cell indices and TSH) across treatment groups over the study duration.

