#### Arm C: combination treatment arm

2.3.3

Patients who are treated at the Ayurvedic hospital but have previously received allopathic treatment will continue to receive allopathic treatment and start new ayurvedic treatment. This arm integrates Allopathic and Ayurvedic treatments, collaboratively managed by both a Psychiatrist and an Ayurvedic specialist. The treatment strategy will be individualized, considering both the patient’s clinical presentation and preferences.

A patient who is already on Allopathic medication (antidepressants) from their psychiatrist and wishes to start ayurvedic treatment would be categorized into this group. The Ayurvedic specialist and the patients treating Psychiatrist would collaboratively decide whether to maintain, reduce, or discontinue the Allopathic medication as the Ayurvedic treatment progresses. If no Allopathic treatment has been initiated, Ayurvedic treatment will be administered for eight weeks before a joint clinical decision is made regarding the addition of allopathic medication. This approach aims to leverage the potential synergistic effects of both treatment modalities, promoting personalized and effective management of MDD. Previous studies have shown that allopathic psychiatric medication can be combined safely with Ayurvedic treatments such as herbs (10, 11, 16–18).

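### The no-difference hypothesis takes in the combination arm, although its premise covers only the two single treatments, and a real benefit of the combination could be reported as agreement with it

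*Protocol article*

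**What the plan says.** The premise stands in section 1.2 (Hypothesis and objectives): "we assume that allopathic and Ayurvedic treatments are equally effective in treating depression". It names the two single modalities and is silent on their combination. The conclusion drawn from it is wider: "we do not expect any statistically significant difference in treatment effect between the treatment groups (between-group effect) in week 8". Section 2.9 repeats it for the groups in general, "We also hypothesize that the groups do not differ in terms of treatment success (between group effect", straight after a sentence about all treatment groups, so Arm C is included.

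The combination is motivated differently. Section 1.1 lists "potential synergistic effects of integrating allopathic and Ayurvedic treatments for MDD" among the things that need to be better understood. Section 2.3.3 says of Arm C: "This approach aims to leverage the potential synergistic effects of both treatment modalities".

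On analysis, section 2.9 compares the three groups by ANOVA or t-tests and also foresees longitudinal models with a group-by-time interaction. Post-hoc comparisons follow only if the groups differ significantly. Effect sizes and 95% confidence intervals are promised for significant findings. No separate hypothesis for Arm C, no equivalence margin and no contrast of the combination with a single modality is stated.

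**The concern.** The hypothesis reaches further than its premise. Equal effectiveness of two treatments given alone says nothing about giving both, and the reason offered for combining them points to a better result in Arm C.

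The wording of the expectation makes this matter. If the prediction is that no significant difference will be found, a non-significant test fulfils it, whether Arm C has no advantage or has one that 35 patients per arm could not show. The reporting rule then leaves the reader without the interval that would separate these two cases. The combination is the part of the study where a difference is most plausible on the authors' own reasoning, so this is where such a misreading is most likely.

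**Working it through.** **The plan's own power figure.** The inputs in section 2.9 are "With a sample size of N = 105 patients, an alpha error probability of 0.5 and a moderate effect size (0.5", with power above 0.8. The abstract gives the arms: "allopathic-only treatment (n=35), ayurvedic-only treatment (n=35), or a combination of both (n=35". The text ties the 0.5 to change from baseline to week 8, which is a within-group effect. A paired t-test with n = 35, d = 0.5 and two-sided alpha 0.05 has noncentrality 0.5 × √35 = 2.96 and power 0.820; 34 patients per arm are needed for 80%. So the stated power is reproduced for the within-group hypothesis in each arm if alpha 0.05 is meant. With 0.5 as printed, power is 0.989. Neither figure says anything about differences between groups.

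**Between groups (illustration).** The plan states no between-group effect. Assume that Arms A and B are equal, that Arm C is better by d standard deviations of the analysed outcome, that there are 35 per arm and that alpha is 0.05. For one-way ANOVA with means 0, 0, d:

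- f = d × √2 / 3
- noncentrality = 105 × f² = 105 × 2d² / 9
- degrees of freedom 2 and 102

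| Assumed d | f | Noncentrality | Power | Probability of a miss |
|---|---|---|---|---|
| 0.3 | 0.141 | 2.10 | 0.229 | 77% |
| 0.5 | 0.236 | 5.83 | 0.558 | 44% |
| 0.8 | 0.377 | 14.93 | 0.936 | 6% |

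**Sensitivity at d = 0.5.**

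- Baseline adjustment replaces d by d / √(1 − r²), where r is the assumed correlation of the baseline covariate with the analysed outcome. For r = 0.5, 0.5 / √0.75 = 0.577, power 0.69, miss 31%. For r = 0.7, 0.5 / √0.51 = 0.700, power 0.86, miss 14%.
- With 28 per arm (assumed 20% loss) and no adjustment, the miss is 54%.
- If alpha were literally 0.5, the miss would be 6%. I take 0.5 as a misprint.

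**Post-hoc step.** In a simulation of 40,000 trials at d = 0.5, a significant F followed by Tukey comparisons showed Arm C better than both other arms in 24%, and better than at least one in 54%.

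**What an interval would add.** For one pairwise contrast the 95% half-width is t(68) × SD × √(2/35). With an assumed SD of 10 MADRS points this is 4.8 points. A non-significant contrast would often still be compatible with a benefit of several points, and the reader would see that only if the interval were reported.

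**Why a better Arm C would not show synergy.** If synergy is taken as more than the sum of the separate effects, the quantity is C − A − B + P, where P is the improvement with neither treatment. No arm supplies P. With the plan's 15-point improvement in A and in B, and 18 points assumed in C, the result is −12, −6, 0 or +3 for P = 0, 6, 12 or 15. Even the sign depends on P.

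**The case against.** Four points can be made for the plan.

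First, the study is called exploratory in sections 1.2 and 2.7 and hypothesis-generating in section 4, and section 3.2 concedes confounding. This limits what will be claimed. It does not remove the stated hypothesis, and an exploratory study has the most to gain from estimates with intervals.

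Second, the miss rate depends on choices the plan does not make. The 0.5 SD between groups is an assumption. Section 2.9 also names mixed-effects models, which can use the baseline value, and a large benefit would seldom be missed. All of this stands, and for this reason a range is given.

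Third, post-hoc comparisons are planned, and the text does not forbid intervals for non-significant results. That is true, but the comparisons are conditional on significance and the intervals are promised only where significance is reached.

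Fourth, taking non-significance for no difference is just as much a problem for Arm A versus Arm B. This stands, and narrowing the hypothesis alone would not cure it.

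A reader might infer something stronger: that the study sets out to test synergy with a design that cannot identify it. The documents do not support this. Synergy appears in the background and in the description of care in Arm C, but in no objective, endpoint or analysis. The additive definition used above is not the plan's, and no synergy claim is announced. The objective in section 1.2 is to compare the two treatments and their combination, which three arms can do.

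**Conclusion.** The point holds as a mismatch between hypothesis, premise and reporting rule. The no-difference expectation includes Arm C without a premise for it and against the motivation given for combining treatments. If the plan is followed as written, a real but moderate benefit of the combination could be reported as agreement with the hypothesis. The probability that the three-group ANOVA misses it is 77%, 44% and 6% for assumed benefits of 0.3, 0.5 and 0.8 SD, and 31% to 14% at 0.5 SD with baseline adjustment at assumed correlations of 0.5 to 0.7. These figures rest on 35 evaluable patients per arm, alpha 0.05, and equal means in Arms A and B. They illustrate the risk and do not measure a shortfall against a target, since the plan sets none between groups.

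Two limits apply to any result for Arm C. Under sections 2.3 and 2.3.3 its patients are selected by earlier allopathic treatment, so contrasts with Arm C are confounded by treatment history. Section 2.3.3 also describes patients in whom no allopathic treatment has been started, who receive Ayurvedic treatment alone for eight weeks, that is, up to the main time point. The two sections must be reconciled on who belongs to Arm C.

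**What to change.** - In sections 1.2 and 2.9, restrict the no-difference expectation to Arm A versus Arm B, and state that a non-significant result will not be read as no difference.
- Report three contrasts in week-8 MADRS change (A minus B, C minus A, C minus B) from the longitudinal model already foreseen, each with a 95% confidence interval whatever the p-value.
- Add one sentence that a better result in Arm C than in Arms A and B will not be read as synergy, because no arm receives neither treatment, and that the contrasts with Arm C are confounded by earlier allopathic treatment.
- Reconcile sections 2.3 and 2.3.3 on membership of Arm C.

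The cost is wording and two or three extra reported contrasts, with no additional patients. The downside is a more modest claim for the combination and intervals that may be wide.

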### Trial design and study setting

2.1

This study employs a naturalistic observational (non-randomization) design, conducted within real-world clinical settings for a six-month period (see **Figure 1**) where the group assignment reflects patient preference and clinical practice in specialized hospitals. The study population comprises 105 adult participants. Participants will be observed in one of three treatment groups, each consisting of approximately 35 individuals, based on the treatment they receive (see **Figure 1**).

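### The power statement treats all 105 enrolled patients as analysed, with no allowance for attrition, and the plan permits repeated-measures ANOVA, which in standard form drops incomplete patients and does not fit its ITT approach

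*Protocol article*

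**What the plan says.** The abstract plans three arms: "allopathic-only treatment (n=35), ayurvedic-only treatment (n=35), or a combination of both (n=35". Section 2.1 repeats the total, "The study population comprises 105 adult participants", in groups "each consisting of approximately 35 individuals".

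The power statement in section 2.9 uses the same total: "With a sample size of N = 105 patients, an alpha error probability of 0.5 and a moderate effect size (0.5". It reports power above 0.8. It names no test, sidedness, standard deviation, dropout rate or evaluable number. The first hypothesis in that section is that every group improves from baseline to week 8.

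On analysis, section 2.9 says: "The primary and secondary outcome measures will be analysed using an intention-to-treat (ITT) and exploratory approach". For the repeated measurements at baseline, week 8, month 3 and month 6 it says that "appropriate statistical models for longitudinal data (e.g., repeated measures ANOVA, mixed-effects models) will be used to analyse changes in outcome measures over time". It adds that ways of dealing with missing data will be considered and documented. Section 2.8 gives the usual right to leave: "Participants will be free to withdraw their consent and discontinue their participation at any time without penalty".

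**The concern.** The number in the power statement equals the number enrolled, so the stated power holds only if every patient has a week-8 MADRS. With 35 per arm the margin may be very thin. The within-arm change at week 8 is the result the trial expects to show, so its stated power should refer to the patients who will be analysed.

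The choice of longitudinal model adds to this. Standard repeated-measures ANOVA needs a complete set of scores for each patient. A patient with a valid week-8 MADRS who misses month 6 would drop out of the model that also gives the week-8 change. Section 2.1 lets patients re-evaluate their treatment at week 8, so later visits could plausibly be missed for reasons linked to response. If non-responders leave, an analysis of completers overstates improvement. Because the arms are non-randomised and tied to two hospitals, it may do so by different amounts in each arm.

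**Working it through.** **Inputs from the protocol article.** Enrolment 105, about 35 per arm (abstract; section 2.1). Effect size 0.5, metric not named (section 2.9). Power above 0.8 (section 2.9). Alpha is printed as "an alpha error probability of 0.5".

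**Assumptions.** Alpha 0.05, two-sided. Paired t-test of baseline against week 8 within one arm. The 0.5 is the mean change divided by the SD of change (dz). The document gives no dropout rate, so a range is shown.

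**Formula.** Noncentrality δ = dz × √n. Power = P(|T| > t(0.975, n − 1)), where T is noncentral t with n − 1 degrees of freedom.

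**Step 1: reproduce the stated power.** With n = 35, δ = 0.5 × √35 = 2.958 and the critical value is 2.032. Power is 0.820, so the claim of more than 0.8 reproduces on this reading. A two-arm t-test with d = 0.5 and 35 per arm gives 0.541, so that reading does not reproduce it at alpha 0.05.

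**Step 2: remove patients.** Numbers left are rounded down.

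| Patients per arm with both scores | Loss from 35 | δ | Power |
|---|---|---|---|
| 35 | none | 2.958 | 0.820 |
| 34 | 1 patient | 2.915 | 0.808 |
| 33 | 2 patients (2/35 = 5.7%) | 2.872 | 0.795 |
| 31 | about 10% | 2.784 | 0.77 |
| 29 | about 15% | 2.693 | 0.74 |
| 28 | 20% | 2.646 | 0.72 |
| 24 | about 30% | 2.449 | 0.65 |

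The smallest number for 0.80 is 34, so one loss per arm is tolerated and two are not.

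**Step 3: other readings of the same sentence.**

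| Reading | Power at full enrolment | Stays above 0.80 down to |
|---|---|---|
| Per-arm paired, one-sided 0.05 | 0.895 | 27 per arm |
| Per-arm paired, alpha 0.5 as printed | 0.989 | 9 per arm |
| All arms pooled, paired, two-sided 0.05 | 0.999 | 34 in total |
| One-way ANOVA, f = 0.5, alpha 0.05 | 0.997 | 42 in total |

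Section 2.9 also equates the effect with a 15-point fall in MADRS. For that to be dz = 0.5, the SD of change would have to be 15 / 0.5 = 30 points. With an assumed SD of change of 10 to 15 points, power is at least 0.98 with only 20 completers per arm.

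**Step 4: complete cases under repeated-measures ANOVA.** Assume complete baselines and independent missingness p at each of the three follow-ups. The complete fraction is (1 − p)³.

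- p = 0.05: 0.95³ = 0.857; 35 × 0.857 = 30.0 per arm. Paired-test power at 30 is 0.754.
- p = 0.10: 0.90³ = 0.729; 35 × 0.729 = 25.5 per arm. Paired-test power at 25 to 26 is 0.67 to 0.69.

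The paired-test power is used here only to show the cost of losing those patients, on the reading of Step 1. Under p = 0.05, about 35 × 0.95 = 33.25 patients per arm would have a week-8 score. Requiring all four scores therefore discards about three more per arm who do have the primary measurement.

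**The case against.** The strongest reply is that the stated figure contains no arithmetic error: it reproduces, at 0.820, on the reading that best fits 35 per arm. A reader might go further and infer that the trial's actual power is below 0.8. The document does not support that. It gives no dropout rate, and the thin margin belongs to one reading of an unnamed test with a substituted alpha. On the other readings in Step 3, most or all of the assumed losses leave the claim intact, and the 15-point target at a plausible SD leaves ample power. This part of the reply stands, and it makes the shortfall conditional.

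A reader might also infer that the plan forecasts missing data. It says only that strategies will be considered, and the withdrawal sentence in section 2.8 is a consent right rather than a forecast. That also stands.

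On the model, the reply is that repeated-measures ANOVA is only an example, that mixed-effects models are named beside it, and that the final choice may be left to an analysis plan. It would be too strong to say that the plan contradicts its own ITT statement outright: the conflict arises only if the ANOVA is chosen and run without imputation across all four time points. But the article presents both models as acceptable. One of them in its standard form does not fit the stated ITT approach, and nothing in the text rules that use out.

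Finally, the study is described as exploratory. That limits the consequences but does not justify a power figure at full retention.

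**Conclusion.** The point holds in two parts.

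First, the power statement counts every enrolled patient as analysed and makes no allowance for attrition. On the within-arm paired reading (dz = 0.5, two-sided alpha 0.05), there is room for one loss per arm. Two losses take power to 0.795; assumed losses of 10% and 20% take it to about 0.77 and 0.72. This depends on the assumed alpha, test, metric and loss rates, so it shows a thin and undeclared margin on that reading. It does not show that the trial is underpowered.

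Second, and on any reading of the power sentence, permitting repeated-measures ANOVA over four time points admits an analysis that drops partly observed patients. That does not fit the ITT approach, and it can bias the week-8 within-arm change towards completers.

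The printed alpha of 0.5 and the equating of an effect size of 0.5 with a 15-point fall are separate and larger problems in the same paragraph. They should be corrected at the same time.

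**What to change.** Two changes in section 2.9:

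1. Delete repeated-measures ANOVA as an option and commit to the mixed-effects model already named. Fit it by REML to all observed MADRS scores, with the change from baseline to week 8 as the primary contrast. Patients who miss month 3 or month 6 then still contribute to the week-8 estimate. The abstract's results paragraph names the same two models and should be brought into line.
2. When the power sentence is corrected, name the test, alpha and sidedness, and give power at the sponsor's expected number per arm with a week-8 MADRS, or over a stated range of losses. If the per-arm paired test at two-sided 0.05 and dz = 0.5 is what was meant, the range runs from 0.82 with no loss to 0.77 at 10% and 0.72 at 20%. These are complete-pair figures, and the sentence should say so.

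The cost is a few sentences and a slightly less favourable stated power. No extra patients or visits are needed.
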